## Abstract

Introduction: Dental caries in the adult population that require preventive and therapeutic treatment are generally neglected in rural communities. The determination of the effectiveness of the application of 38% silver diamine fluoride (SDF) in arresting caries lesions when combined with atraumatic restorative treatment (ART) is very important, as it serves as a preventive and restorative procedure to regain the function of the permanent dentition. The assessment of optimal SDF application with ART, in comparison with ART alone, in managing cavitated carious lesions in a pragmatic setting, is the need of the hour to recommend optimal dental care, especially in rural settings which have minimal access to comprehensive dental care. Methods and Analysis: The clinical trial will enrol 220 adults (18–65 years) with cavitated carious lesions attending the Amrita School of Dentistry in the Ernakulam district, India. This study is a randomized, controlled trial with a 1:1 allocation ratio in two parallel groups. Study arm 1 will receive 38% SDF application and ART, and study arm 2 will receive ART only. A digital radiograph will be taken immediately after restoration (baseline) as well as at the end of the 6th month for evaluation of caries arrest. The assessment of the survival of the restoration will be done on the 7th day, 30th day, and at the end of the 6th month. The final analysis would include both the tooth and person levels. Ethics and Dissemination: This trial adheres to the principles of the Declaration of Helsinki and the guidelines of the Indian Council of Medical Research (ICMR). This study protocol has been approved by the Institutional Review Board. This trial has been registered prospectively with the Clinical Trial Registry of India (Registration No: CTRI/2021/12/038816).

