## 2. Methods

### 2.1. Study Design

This is a randomized, controlled trial with two parallel comparator arms, having a 1:1 allocation ratio (Figure 1).

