### 2.4. Study Population

Any individual between 18 to 65 years with one or more cavitated carious lesions in the occlusal and/or proximal surface of the permanent posterior teeth.

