### 2.12. Study Implementation

The adult patients visiting for routine dental care to dental school will be recruited for the study. A clinical examination will be carried out on prospective participants. If the individual satisfies the inclusion criteria, the participant will be informed of the options for caries prevention by ART ± SDF. If they agree, they would be offered the choice of participation in the trial and the consenting process will be followed. The patient screening will continue till the target population is attained (n = 220).

Enrolment of the study population will be done over 24 months and follow-up visits are expected to be completed at the end of the 30th month, which will be followed by analysis and report writing. The total study duration is of three years.

The selected participants for the trial will be randomly allocated to a study arm, as per computer-generated randomization. The randomization code will not be revealed to the principal investigator until the participant has been recruited into the clinical trial after all the baseline assessments are complete. This is to ensure allocation concealment. Opaque-sealed envelopes containing randomization codes, in compliance with the randomization list, will be employed for allocation concealment. The randomization will be conducted by the research assistant. The randomization list will remain with the trial coordinator for the whole duration of the research. Due to the apparent nature of the treatment involved, neither the study participant nor the principal investigator (PI) can be blinded.

The PI will be trained for the study requirements, standardized in the assessment of the coronal carious lesion, caries cessation, 38% SDF application and ART, or ART alone, eliciting the required details from the study subjects in a consistent replicable method, and counseling for compliance. The procedure to be conducted and the data to be collected at each study visit will be inspected in detail. During the training sessions, details about procuring and entering the quality data in the clinical record forms will also be discussed. Calibration of PI (AV) will be done before and during the study by another clinical expert (CJ) and reliability will be expressed using Cohen’s kappa statistic.

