## 4. Statistical Methods

The observed data will be coded, tabulated, and analyzed using Statistical Package for Social Sciences (version 20). We will assess the outcomes at two levels (the Tooth level and the Individual level). The Chi-square test will be executed to assess the bivariate association between the outcome and sociodemographic variables. Kaplan–Meier survival analysis will be conducted on the censored data for the survival of the restoration. The difference between survival curves will be assessed by the Mandel—Haenszel log-rank test. Factors affecting survival rates will be assessed using the Cox-proportionality regression method. Between the two groups, the arrest of active carious lesion and survival of the restoration will be compared on the 7th day, 30thday, and at the end of the 6th month of the study visit. If there is a variation in outcome in patients with multiple restorations, tooth level analysis will be carried out.

Subgroup analysis will be performed at the tooth level (type of cavity; class1 and class 2, maxillary and mandibular teeth, premolar and molar)

We intend to have two sets of analyses.

The intention-to-treat analysis (including all randomized patients irrespective of whether they have or have not received the prescribed treatment).The per-protocol analysis.

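### Patients are randomised and may have several treated teeth, but the use of tooth-level analysis depends on the observed outcomes and no allowance for within-patient correlation is stated

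*Protocol article*

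**What the plan says.** The unit of randomisation is the patient. Section 2.12 (Study Implementation) states: "The selected participants for the trial will be randomly allocated to a study arm, as per computer-generated randomization". Section 2.1 gives two parallel arms at 1:1.

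A patient can supply more than one tooth. Section 2.4 admits individuals "with one or more cavitated carious lesions in the occlusal and/or proximal surface of the permanent posterior teeth", with no cap. Section 2.7 speaks of treating selected teeth in the plural, and Section 4 refers to patients who have multiple restorations. All of a patient's study teeth follow that patient's allocation.

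On the level of analysis there are three statements:

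- Abstract: "The final analysis would include both the tooth and person levels".
- Section 4, early: "We will assess the outcomes at two levels (the Tooth level and the Individual level". Neither level is called primary.
- Section 4, later: "If there is a variation in outcome in patients with multiple restorations, tooth level analysis will be carried out".

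For restoration survival, Section 4 names Kaplan-Meier curves, then "The difference between survival curves will be assessed by the Mandel—Haenszel log-rank test", then "Factors affecting survival rates will be assessed using the Cox-proportionality regression method". Subgroup analyses by cavity class, jaw and tooth type are placed at tooth level. Chi-square is assigned to associations between outcome and sociodemographic variables. No between-arm test is named for caries arrest. The article does not mention clustering, frailty, robust variance, GEE, a mixed model or an ICC, and does not say how several teeth combine into one patient-level outcome.

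**The concern.** Teeth in one mouth share diet, hygiene, caries risk and usually the treatment session, so their outcomes are likely to be positively correlated. Because whole patients are allocated, that correlation adds directly to the variance of the arm comparison. A log-rank test or Cox model that counts each tooth as a separate observation leaves the extra variance out. Its standard error is then too small and its type I error too high.

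The conditional sentence is a separate weakness. It lets the observed outcomes decide whether the tooth-level analysis is done, and it does not say how much variation is enough. With no primary level named, a reader of the results could not tell which of two answers had been fixed beforehand.

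Both primary outcomes, restoration survival and radiographic caries arrest, are recorded on teeth. The main treatment comparison is therefore exposed, not only the subgroups.

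**Working it through.** **1. The plan's own sample size.** Inputs from Section 2.11: effect size 0.4, alpha 0.05, power 80%, 100 per group, 10% attrition, 110 per group. The type of effect size and the sidedness are not stated. I read them as a standardised mean difference and a two-sided test.

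n per group = 2 × (1.960 + 0.842)² / 0.4² = 98.1, so 99 by the normal approximation. The noncentral t gives 99.08, so 100. Then 100 × 1.1 = 110 (dividing, 100 / 0.9, would give 112). The stated figure reproduces with the patient as the unit. It contains no design effect, and needs none if patients are the unit.

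**2. Error of an unadjusted tooth-level test.** Teeth per patient (m) and the ICC are my assumptions, because the document gives neither.

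Design effect: DE = 1 + (m − 1) × ICC.
True two-sided error of a nominal 5% test: 2 × [1 − Φ(1.96 / √DE)].

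Example, m = 2 and ICC 0.3: DE = 1 + 1 × 0.3 = 1.3; 1.96 / √1.3 = 1.72; error = 8.6%. The 200 teeth per arm carry the information of 200 / 1.3 = 154 independent teeth.

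| Teeth per patient | ICC 0.1 | ICC 0.3 | ICC 0.5 |
|---|---|---|---|
| 1 | 5.0% | 5.0% | 5.0% |
| 1.25 | 5.3% | 5.9% | 6.5% |
| 1.5 | 5.6% | 6.8% | 8.0% |
| 2 | 6.2% | 8.6% | 11.0% |
| 3 | 7.4% | 12.1% | 16.6% |

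From m = 1.25 to m = 3, the naive standard error is 0.99 to 0.71 of the true one (1/√DE).

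The formula assumes the same number of teeth in every patient, so it is slightly low for a fractional mean. With unequal numbers, m is replaced by the sum of m² over the sum of m. If 75% of patients have one tooth and 25% have two, this is (0.75 + 1.00) / 1.25 = 1.4. DE is then 1.04 to 1.20 and the error 5.5% to 7.4%, against 5.3% to 6.5% in the table.

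**3. Check by simulation.** Settings: beta-binomial tooth failures, 100 patients per arm, 20,000 runs, assumed failure rate 20%, no arm effect, and a comparison of proportions standing in for the survival test.

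| Share of patients with 1/2/3 teeth | ICC | Naive tooth-level | Cluster-robust | Patient-level (any failure) |
|---|---|---|---|---|
| 70/20/10% | 0.1 | 6.0% | 5.4% | 5.2% |
| 70/20/10% | 0.3 | 7.6% | 5.2% | 4.8% |
| 70/20/10% | 0.5 | 9.1% | 5.2% | 4.7% |
| 50/30/20% | 0.1 | 6.5% | 5.4% | 5.3% |
| 50/30/20% | 0.3 | 8.6% | 5.2% | 4.8% |
| 50/30/20% | 0.5 | 11.4% | 5.3% | 5.0% |

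Allowing for the patient brings the error back close to 5%. The patient-level test was never materially wrong.

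**4. The conditional rule.** In the same simulations at least one patient with discordant teeth occurred in essentially every trial. If one such patient is enough to count as variation, the rule almost always leads to the tooth level. If more is needed, the protocol does not say how much.

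**The case against.** Four points can be made for the protocol.

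First, it nowhere says that teeth are independent. It names families of methods, and a robust variance or a frailty term is the kind of detail a condensed article may leave to an analysis plan that is not shown. This stands in part. Independence is inferred from the standard form of the named methods, so the optimism must be stated conditionally. It does not rescue the conditional sentence, which is written into the protocol and which an analysis plan following it would inherit.

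Second, a reader might infer that every listed test, chi-square included, is to be run on teeth to compare the arms. The text does not support that. Chi-square is tied to sociodemographic associations, the survival methods carry no label of level, and no arm comparison of caries arrest is named. Only the conditional sentence and the subgroups are explicitly at tooth level.

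Third, a reader might infer that the unit will be picked to suit the result. The trigger is disagreement between teeth within a patient, not the arm difference, and the sentence can be read as adding a tooth-level analysis where one patient-level result would hide discordant teeth. If significance at either level counted as success, the simulated error was 7.4% to 17.9%, but the document does not say that either level would count. Those figures describe a risk left open by naming no primary level, not a stated plan.

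Fourth, much of the procedural text speaks of a single tooth, and if most patients have one, the inflation is slight. That is correct and belongs in any statement of size.

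**Conclusion.** The point holds in conditional form. The protocol randomises patients, permits several teeth each, makes tooth-level analysis depend on the observed outcomes without a threshold, names no primary level, and contradicts its own abstract on whether both levels are always analysed. If the named survival methods, or the tests in the tooth-level subgroups, are applied to teeth in standard form, their p-values and intervals are too optimistic whenever some patients have more than one tooth and those teeth are positively correlated.

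The size cannot be calculated from the document. Over the assumed range it runs from barely noticeable, when few patients have a second tooth, to more than three times the nominal level at three teeth each and an ICC of 0.5. It is nil with one tooth each or no correlation.

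Two wider conclusions do not follow. The planned individual-level analysis is not affected by clustering, although its outcome still needs a definition for patients with several teeth. The sample size is not shown to be wrong, since 100 per group reproduces for patients. The fault lies in the inference at tooth level and in the rule that leads there.

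**What to change.** - Delete the conditional sentence in Section 4. Name one primary unit of analysis in advance, in the same terms in the abstract and Section 4.
- Tooth-level restoration survival: a Cox model for arm with patient-level robust variance or a shared frailty per patient, in place of the plain log-rank test. Kaplan-Meier curves can stay as description.
- Tooth-level caries arrest: a logistic GEE or mixed model clustered on patient.
- Tooth-level subgroups (cavity class, jaw, tooth type): the same clustered models with an arm-by-subgroup term.
- Keep the individual-level analysis, and define how several teeth form one patient outcome, for example any failed restoration.

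Covariate adjustment is optional and is not part of this correction, because it does not repair clustering.

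The cost is a change of wording, slightly more analysis work and somewhat wider tooth-level intervals. No extra patients or visits are needed, and trial conduct does not change.

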## 5. Analysis of Population and Missing Data

The reasons for participant withdrawal would be qualitatively compared for each randomization group and reported. The effect of missing data on the results will be assessed using sensitivity analysis of the augmented data sets. The individual dropouts will be included in the analysis, which would be carried out by multiple imputation methods for missing data.

## 6. Patient and Public Involvement

The dissemination of appropriate dental care concepts through community health workers in an easily understandable way can bring a drastic change in the general perception of oral health. This can be further achieved through the advancement of community-based procedures such as atraumatic restorative treatment, a non-aerosol generating procedure, and the application of silver diamine fluoride. For arresting the progression of caries and restoration of the function of a decayed tooth, a combination of 38% silver diamine fluoride along with atraumatic restorative treatment would be a new minimally invasive method, which can be carried out using simple hand instruments. This combination of ART and SDF may be an effective method to prevent and treat dentinal caries in the adult population, especially among those with disability and poor general health.

The study design (randomized controlled trial) will provide evidence of caries arrest following a novel combination technique of restoration with silver diamine fluoride along with atraumatic restorative treatment on the cavitated tooth. The assessment of optimal SDF application with ART, in comparison with ART alone, in managing cavitated carious lesions in a pragmatic setting, is the need of the hour to recommend optimal dental care, especially in rural settings which have minimal access to comprehensive dental care. This trial is designed to address this knowledge gap. If the trial is successful, the impact would be a change in the standard of care and provide greater access to a non-invasive, simple, and inexpensive strategy to manage cavitated caries lesions, thereby helping to reduce pain and associated dental problems in the adult population.

## 7. Ethics and Dissemination

This trial adheres to the principles of the Declaration of Helsinki and the guidelines of the Indian Council of Medical Research (ICMR). The study protocol has been approved by the Institutional Ethics Committee (IEC) of Amrita Institute of Medical Sciences, AIMS, Kochi, India (IEC-AIMS-2021-DENT-280). Following the completion of the trial, an end-of-trial notification and final report would be submitted to IEC, AIMS.

Informed consent would be obtained from the participants by the principal investigator. A printed information sheet and a copy of the consent in the patient’s native language/English would be provided to the participants with sufficient time for them to discuss the trial and decide on their participation. The participant would be made aware of their responsibilities and their right to withdraw participation from trial at any time without prejudice to future care and without citing any reason whatsoever. Any data that breaches the blind will not be presented until the completion of the trial, in order to maintain the integrity of the study. The informed consent form indicates that individual patients’ data may be used for publication purposes. During and upon completion of the study, only the study investigators will have access to the data. Three years after the completion of the trial, de-identified data will be shared with a data archive source. The relevant study results and actionable points will be shared with concerned health authorities.

## Figures and Tables

**Figure 1 mps-05-00087-f001:**
[figure not shown]
Study flow diagram.

**Table 1 mps-05-00087-t001:** Participant timeline.

	Enrolment	Allocation	Post Allocation			Close Out
Time Point	t-1	t0	t1 (7 days)	t2 (30 days)	t3 (6 months)	tx
*Enrolment*						
Eligibility screen	X					
Informed consent	X					
Allocation		X				
Caries excavation		X				
*Interventions*						
38% SDF + ART						
ART						
*Assessments*						
Baseline variables cavitated carious lesion	X		X	X	X	
Caries arrest			X	X	X	X
Survival of restoration			X	X	X	X

## Data Availability

Data sharing does not apply to this article as it is a study protocol.

## Abbreviations

SDF–silver diamine fluoride, ART–atraumatic restorative treatment, AIMS–Amrita Institute of Medical Sciences, IRB–Institutional Review Board.
